#### Mediation analysis

A causal mediation analysis will be performed to guide graded motor imagery optimisation and implementation. This analysis will estimate the effects of graded motor imagery on pain intensity and pain interference through the putative mediators [62].

#### Complier average causal effect

If there is significant non-adherence with the allocated interventions, we will estimate the complier-average causal effect (CACE) using instrumental variable estimation [63, 64]. For the purposes of the CACE analysis, we will define memantine adherence as taking 80% or more of the prescribed dose (self-reported), and graded motor imagery adherence as attendance at 5 or more of 7 sessions.

### Methods in analysis to handle protocol non-adherence and any statistical methods to handle missing data {20c}

The analyses are based on the intention-to-treat principle, where all participants will be assessed in the groups to which they are randomised, regardless of the intervention received or intervention adherence. A summary of the interventions allocated and received will be reported for each comparison. Details on the presentation of intervention adherence and protocol deviations are provided in Appendices 1 and 2 and Supplementary Tables 7 and 8.

Efforts will be taken to minimise the amount of missing outcome data (see Plans to promote participant retention and complete follow-up {18b}). For each outcome, the amount of missing data will be reported. The nature and pattern of data missingness will be explored to determine, as far as is possible, whether data can be treated as missing completely at random (MCAR) or missing at random (MAR). If more than 10% of the primary outcome data are missing and the MAR assumption appears plausible, a sensitivity analysis will be conducted in which the main analysis is replicated using multiple imputation [65, 66].

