
Continuous outcomes will be assessed as differences in mean final values at each timepoint; binary outcomes will be assessed as ratios of proportions.

PROMIS instruments use a *T*-score metric, in which 50 is the mean of the reference population and 10 is the standard deviation of that population [51]. All PROMIS scales, except for Global Health short form v1.1, will be measured using computer adaptive tests. Computer adaptive tests use item response theory to provide precise measurement using few items, and allow for scores that are directly comparable across different selections of items [52].

Pain intensity, pain interference, physical function, self-efficacy, and cognitive function will also be measured at 12 weeks to explore the mechanisms by which the graded motor imagery intervention exerts its effects. To evaluate the effect of adhering to the interventions, the following outcomes will also be measured: weekly measures of pain intensity, item 4 of the Credibility/Expectancy Questionnaire [53], Medical Form Confidence (weekly); International Physical Activity Questionnaire Short Form [54] (end of treatment only). See Methods for additional analyses (e.g. subgroup analyses) {20b} for further information.

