### Sample size {14}

The sample size calculation was based on a factorial analysis, where interventions are assumed to have independent effects. For the primary outcome of pain intensity at 16 weeks, we will be guided by a between-group difference of 1 point on an 11-point NRS to justify implementation of the interventions as suggested for chronic pain RCTs [55]. For the primary outcome of pain interference at 16 weeks, we will be guided by a between-group difference *T*-score metric of 5 to justify implementation of the interventions.

Using a repeated measures model with outcomes measured at baseline and follow-up timepoints, and with a correlation between adjacent time points of 0.7 [56], 182 participants are required to provide 90% power with a two-sided 2.5% significance level to detect an effect (of memantine compared to placebo, or graded motor imagery compared to no graded motor imagery) of either 1 point on an 11-point NRS for pain intensity, assuming a standard deviation of 2, or 5 *T*-metric points on the PROMIS Pain Interference scale, assuming a standard deviation of 10. Allowing for 10% dropout, we will aim to recruit a total of 204 participants (rounded up from 200.2).

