### Statistical methods for primary and secondary outcomes {20a}

#### Main analysis

All outcomes will be analysed according to the intention to treat principle. The analysis will involve estimation of the marginal mean effect of memantine compared to placebo and the marginal mean effect of graded motor imagery compared to no graded motor imagery on pain intensity and pain interference at 16 weeks. Additional information on the estimands of interest, including handling of intercurrent events, is provided in Table 2. As the trial has dual primary outcomes, interval estimates will be 97.5% confidence intervals. There will be no multiplicity adjustment for the two interventions as the factorial design answers two distinct questions.

**Table 2 Tab2:** Trial estimands

Estimand component	Definition
Interventions to be compared	To estimate the average causal effect of memantine, we will compare the mean outcome of trial participants allocated to receive memantine and graded motor imagery or memantine only with the mean outcome of trial participants allocated to receive placebo and graded motor imagery or placebo only To estimate the average causal effect of graded motor imagery, we will compare the mean outcome of trial participants allocated to receive memantine and graded motor imagery or placebo and graded motor imagery with the mean outcome of participants allocated to receive memantine only or placebo only
Population of interest	Adults with CRPS as defined by the trial eligibility criteria
Outcome of interest	Pain intensity, measured on a 11-point NRS; pain interference, measured with PROMIS pain interference v1.1
Summary measure (population-level)	Mean difference
Intercurrent events	All intercurrent events relating to memantine and graded motor imagery (e.g. intervention discontinuation, use of non-trial treatments) will be handled using a treatment policy strategy

For each of the dual primary outcomes, we will fit a longitudinal mixed-effects model that includes terms for the fixed effects of each intervention, the three follow-up timepoints, the intervention by time interactions, the two-way interaction between the interventions, and the baseline values of the outcome variables. In addition, the models will include terms for the fixed effects of the duration of CRPS (modelled as linear or linear with log transformation) and workplace compensation status, as well as random intercepts for trial participants.

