### Methods for additional analyses (e.g. subgroup analyses) {20b}

#### Sensitivity analyses

Sensitivity analyses will be conducted to assess the impact of deviations to the ‘no interaction’ assumption on the primary outcomes. As recommended by Kahan et al. [59], the size, confidence intervals, and *p* value of the treatment-by-treatment interaction will be inspected to assess the plausibility of the assumption of no interaction underpinning the interpretation of the marginal estimator. Further sensitivity analyses will be conducted on the primary outcomes to estimate the effects of each intervention conditional on the presence or absence of the other intervention, again using the -margins- command in Stata. The effect of each intervention combination (memantine and graded motor imagery; memantine only; graded motor imagery and placebo) compared with the double control group (placebo only) will also be estimated (Supplementary Table 6). Multi-arm analyses remain unbiased even when interventions interact [59].

The analyses described below may be reported in secondary publications.

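### The only missing-data sensitivity analysis again assumes MAR and runs only when MAR looks plausible, so the plan cannot show whether a primary result survives outcome-dependent dropout

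*Protocol article*

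**What the plan says.** The article's section on non-adherence and missing data ({20c}) has missingness explored to judge, so far as the data allow, "whether data can be treated as missing completely at random (MCAR) or missing at random (MAR"). It then sets a two-part condition: "If more than 10% of the primary outcome data are missing and the MAR assumption appears plausible, a sensitivity analysis will be conducted". The analysis meant there is one "in which the main analysis is replicated using multiple imputation". MNAR is not named, and no analysis is given for the case where MAR does not look plausible.

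The Main analysis section says "we will fit a longitudinal mixed-effects model that includes terms for the fixed effects of each intervention", with time, interactions, baseline outcome, CRPS duration, compensation status and random participant intercepts. In Table 2, intercurrent events "will be handled using a treatment policy strategy".

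The section headed Sensitivity analyses concerns another matter: "Sensitivity analyses will be conducted to assess the impact of deviations to the" no-interaction assumption. The complier-average analysis concerns adherence. Neither deals with missing outcomes.

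The Outcomes section also provides for "weekly measures of pain intensity" and for both primary measures at week 12. No missing-data analysis is said to use them.

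**The concern.** A missing-data sensitivity analysis should vary the assumption that the main analysis cannot verify. Here that assumption is MAR: given treatment, covariates and observed outcomes, whether a week-16 score is missing does not depend on its value. Multiple imputation of the same analysis under MAR leaves that assumption in place. If the two analyses agree, a reader may take this as reassurance about informative dropout when it is not.

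The risk is realistic in this trial. Participants may withdraw from outcome assessment altogether ({18b}), and the graded motor imagery comparison is unblinded with self-reported primary outcomes ({17a}). If those who are doing worse than their recorded data predict are the ones who leave, and this differs between levels of a factor, the estimated effect shifts. The General analysis principles rest interpretation on point estimates and their precision, so such a shift bears directly on the trial's stated aim.

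**Working it through.** **1. The plan's own attrition figure.** Sample size {14} states that "182 participants are required to provide 90% power with a two-sided 2.5% significance level" and then allows for 10% dropout.

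- 182 × 1.10 = 200.2, which is the stated figure; the target is 204, a multiple of the four groups.
- Dividing instead, 182 / 0.90 = 202.2, so 203. The target of 204 covers both formulas.
- 204 × 0.90 = 183.6, so the recruitment target is adequate for 10% loss.

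**2. The trigger against that allowance.** The sensitivity analysis needs more than 10% missing. With 204 randomised, 20 missing is 20/204 = 9.8% (no analysis) and 21 missing is 21/204 = 10.3% (analysis possible). Attrition at the planned rate therefore sits at the threshold and would prompt nothing.

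**3. Does the planned imputation test anything different?** A mixed model fitted by likelihood is valid under MAR given its terms, and standard multiple imputation also assumes MAR. A simulation compared the two. All of its settings are assumptions: 204 participants, true effect −1.0, SD 2, correlation 0.7 between adjacent visits, more dropout before week 16 in the treated arm, no auxiliary variables, 150 replicates, Monte Carlo standard error about 0.02.

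| Dropout mechanism | Missing | Mixed model | MAR imputation |
|---|---|---|---|
| MAR (depends on arm and baseline) | 15% | −1.02 | −0.99 |
| MNAR (depends on unseen week-16 score, treated arm) | 13% | −1.22 | −1.19 |

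The methods differ by less than 0.03 points in both cases. Under MNAR both are about 0.2 points too favourable, and their agreement does not reveal it. This is one assumed mechanism, so it illustrates the problem and does not forecast the bias.

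**4. Size of a departure from MAR.** Let f be the fraction missing at week 16, and delta the number of points by which missing outcomes are worse than MAR predicts. Then

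shift = f(active) × delta(active) − f(control) × delta(control).

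The documents give neither f by arm nor delta, so these values are assumed.

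| f active / control | delta active / control | Shift (NRS points) |
|---|---|---|
| 10% / 10% | 1 / 1 | 0.10 − 0.10 = 0 |
| 10% / 10% | 1 / 0 | 0.10 × 1 = 0.10 |
| 20% / 10% | 1 / 1 | 0.20 − 0.10 = 0.10 |
| 10% / 10% | 2 / 0 | 0.10 × 2 = 0.20 |
| 20% / 10% | 2 / 0 | 0.20 × 2 = 0.40 |

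**5. Against the design precision.** Detecting 1 point with 90% power at two-sided 2.5% implies a standard error of 1 / (2.241 + 1.282) = 0.284, and a 97.5% confidence interval half-width of 2.241 × 0.284 = 0.64. A shift of 0.10 is 10% of the target difference and 0.10 / 0.64 = 16% of the half-width. A shift of 0.40 is 40% of the target and 0.40 / 0.64 = 63% of the half-width.

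Pain interference is planned at the same standardised difference (5/10 = 1/2), so the same proportions hold. For example, 20% missing with delta 10 in one arm shifts the effect by 2.0 T-score points, 40% of the 5-point target.

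**The case against.** Several stronger readings are tempting, and the documents do not support them.

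- **That the rule is backwards.** Making a MAR imputation conditional on MAR being plausible is coherent, because the imputation would not be valid otherwise. The defect is that the other branch is empty and the condition cannot be checked from the data. The text itself concedes that limit.
- **That dropout related to arm biases the main analysis.** Treatment is in the model, so dropout that depends on arm alone, or on arm plus modelled data, is MAR. Bias needs dependence on the unseen outcome given those terms.
- **That stopping treatment means losing data.** Under {18b}, participants who stop treatment are asked whether they will continue assessments, with reminders and calls. The treatment policy strategy uses what they provide.
- **That the imputation can add nothing.** With week-12 or weekly scores as auxiliary variables it would rest on a weaker MAR assumption than the main model. That would be useful, but no auxiliaries are named, the text speaks of replicating the main analysis, and the result would still be a MAR analysis.
- **That the intention-to-treat statement is broken because a participant with no outcome at weeks 16, 26 or 52 contributes nothing to the model.** The sentence concerns the group in which people are analysed. It does not promise that everyone supplies data, and the planned flow diagram reports exclusions from analysis.

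It might also be said that an unseen analysis plan covers this. The article's title and Trial status section say that it includes the statistical analysis plan, and the point concerns a rule that is stated, not one left out.

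These objections narrow the point and lower its severity. They do not supply an analysis that relaxes MAR.

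**Conclusion.** The point holds in a limited form. As written, the plan has one missing-data sensitivity analysis. It shares the main model's untestable assumption, runs only if that assumption looks plausible, is not triggered at the planned dropout rate, and has no counterpart when MAR is doubted. The plan therefore cannot show whether a primary result survives dropout that depends on unseen outcomes.

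The plausible size runs from nothing to 0.40 NRS points against a 1-point target, wholly under assumed missingness and deltas. A reader might take 0.40 as the expected bias. It is not: it needs 20% missing in the active arm (twice the planned rate), a departure of one full assumed SD, and no departure in control. At 10% missing with delta 1 in one arm the shift is 0.10. The estimand, the main model and the primary estimate are unaffected, so this is a should-fix improvement to a supporting analysis.

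**What to change.** In {20c}, remove the MAR-plausibility condition and the 10% trigger. Before unblinding, prespecify the following for both primary outcomes at week 16:

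- **Method:** delta-adjusted (pattern-mixture) multiple imputation, from delta zero (the MAR case) upward in the direction of worse outcome, reporting the tipping point. The team should justify the upper end; one assumed SD (2 NRS points, 10 T-score points) is a natural candidate.
- **Factorial rule:** for each main comparison, apply delta to missing values by that factor's level, once at the active level only and once at both levels, with the other factor's delta held at zero. This settles what happens in the combined group.
- **Auxiliary variables:** include the week-12 outcomes and the weekly pain scores in the imputation model.

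No new data are needed. The cost is revised wording, extra programming and a few supplementary tables; the primary analysis is unchanged. Final assessment is expected in Q2 2027, so there is time to fix the deltas before allocations are known; chosen later, they would be open to the charge of being data-driven.

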### Plans to give access to the full protocol, participant-level data, and statistical code {31c}

A data sharing plan will be established in accordance with Australian New Zealand Clinical Trials Registry requirements. This includes provisions for sharing de-identified participant-level data, the full trial protocol, participant information forms, ethical approvals, and analytic code, subject to participant consent and regulatory requirements. Requests for de-identified participant-level data or analytic code will be reviewed to ensure they align with the study’s data use agreements.

## Oversight and monitoring

### Composition of the coordinating centre and trial steering committee {5d}

MEMOIR is sponsored by Neuroscience Research Australia. The coordinating study centre at Neuroscience Research Australia will perform all recruitment, screening, and monitoring activities. A dedicated trial manager will oversee all aspects of daily trial conduct, assist with governance and regulatory matters, and provide quality control. A Trial Management Committee, comprising the chief investigator, trial manager, and research assistants, will meet monthly to ensure the project delivers its objectives, and monitors the project’s budget, schedule, milestones, and risks.

A Trial Steering Committee will be formed, comprising scientific experts with content and methodological expertise, medical training, and consumers. Chair and co-chair positions will be appointed. The Trial Steering Committee will be responsible for the general oversight of the study, providing scientific advice regarding all aspects of the study design, protocol development, conduct, and data collection. The Trial Steering Committee will develop, approve, and maintain the Trial Steering Committee Charter. The MEMOIR Trial Steering Committee will be the decision-making body responsible for implementing modifications to the protocol, including those that result from recommendations from the study’s DSMB. Trial Steering Committee meetings will take place every 6 months.

### Patient and public involvement and engagement

A consumer panel was formed prior to the commencement of the study. The panel includes people who have or have recovered from CRPS and consumer advocates. The panel is responsible for the provision of participant-relevant recommendations for aspects of the trial including development and conduct, quality control, and community engagement. The MEMOIR investigators provided external consumer training to all members. Over a series of focus groups, the panel informed critical features of the study including the research question, the acceptability of the screening procedures and trial interventions, and the selection of primary and secondary outcomes. During the conduct of the trial, the panel will oversee study processes and review media briefs to ensure appropriate content and language. The panel will be involved in the interpretation and dissemination of study results and will develop a lay language summary of trial results. The consumer contributions to the study will be reported in the published manuscript. A separate group of five people with lived experience of CRPS was involved in the development of the CRPS Handbook. This involvement included initial brainstorming about illustrations and the use of metaphors, iterative review of text, and final review of combined text and illustrations. Data from other people diagnosed with CRPS, presented in full elsewhere [67], were also integrated into that trial-specific patient handbook.

### Composition of the data monitoring committee, its role and reporting structure {21a}

A DSMB will be appointed to review the safety and progress of the trial. The DSMB will comprise a chair and three members with clinical or statistical expertise, all independent from the sponsor and competing interests. The DSMB will review accumulating unblinded safety data (intervention withdrawals, adverse events, and serious adverse events) at regular intervals and advise the Trial Steering Committee Chair if any change to the study is recommended. The DSMB reports directly to the Trial Steering Committee Chair, who liaises with the Trial Steering Committee on any recommendations.

### Adverse event reporting and harms {22}

Safety monitoring and reporting will be conducted in accordance with the NHMRC guidance on Safety Monitoring and Reporting in Clinical Trials Involving Therapeutic Goods and the International Council for Harmonisation Good Clinical Practice guidelines [36, 68]. Adverse events will be collected by active capture (weekly during treatment [weeks 1 to 16] and during follow-up [week 26, week 52]), or by passive capture (participant report via telephone, email, or SMS). Data on adverse effects specific to memantine (those listed on the memantine product information), new medical conditions, or the worsening of existing medical conditions will be collected. Each adverse event reported will be assessed for:Seriousness: any medical occurrence that results in death; is life-threatening; requires inpatient hospitalisation or prolongation of an existing hospitalisation; results in persistent or significant disability/incapacity; is a congenital anomaly or birth defect; or is medically significant or important event or reactionCausality: whether the event has a reasonable causal relationship to the trial interventionExpectedness: whether the event is listed in the memantine product informationSeverity: mild/moderate/severe

The DSMB will periodically review overall safety data to determine trends of events or identify safety issues that would not be apparent on an individual case basis. A safety management plan will outline the flow and timelines for reporting all relevant safety information between the coordinating centre, the sponsor, the Human Research Ethics Committee, and the Australian Therapeutic Goods Administration.

### Frequency and plans for auditing trial conduct {23}

All trial procedures are outlined in study manuals to ensure compliance with the protocol and ICH Good Clinical Practice guidelines. Audits will be conducted by a staff member at the advice of the Steering Committee and will concern enrolment, consent, eligibility, adherence to trial interventions, policies to protect participants (including reporting of harm), and completeness, accuracy, and timeliness of data collection. An external audit, independent from the investigators and the sponsor, will be conducted before commencing the trial and during its conduct.

